##### Patient-reported anxiety and depression symptoms

Assessed with the Hospital Anxiety and Depression scale (HADS). The HADS is a 14-item measure of self-reported symptoms of anxiety (7 items) and depression (7 items) [44]. Each item is scored from 0 to 3, indicating absence of symptoms or presence of positive features (0) to maximal presentation of symptoms or the absence of positive features [3]. The HADS has been validated and found to have good psychometric properties [45, 46].

##### Patient-reported physical disability

Assessed with the Disability Rating Index (DRI). The DRI is a self-assessment measure of experienced physical disability by patients with musculoskeletal disorders. It includes twelve consciously unspecified everyday activities that the vast majority of people perform or can imagine. The questions are arranged in order of increasing physical demands, where the participants mark on a 100-mm visual analogue scale (VAS) in accordance to her/his presumed ability to perform the daily physical activities in question. The anchor points are “without difficulty” = 0 and “not at all” = 100. The instrument has good reliability, validity and responsiveness [3].

##### Drug consumption

Consumption of pharmaceutical drugs that can be related to the musculoskeletal condition for which the participant is treated (ATC codes M – musculoskeletal system and N – nervous system) will be estimated using data from the Swedish registry for drug use, regarding filled prescriptions. Data will be collected for a 3-month period before baseline and for the 12-month period after baseline. Self-reported drug consumption, both prescription and nonprescription drugs, will be collected via the questionnaire.

Other secondary outcome measures are loss of productivity and healthcare costs and incremental cost-effectiveness ratios [17].

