### Aims

The aim of the study is to evaluate effects of an early intervention, the PREVSAM model, on the prevention of sickness absence and development of persistent pain in at-risk patients with musculoskeletal pain. The study will also evaluate effects of the PREVSAM model on patient-reported work ability, risk for sickness absence, musculoskeletal pain status, self-efficacy, health-related quality of life, physical disability, depression and anxiety symptoms, and drug consumption. Cost-effectiveness of the model will be evaluated.

Research questions:

Q1: Is the PREVSAM model more effective in preventing sickness absence, compared with treatment as usual, in patients with musculoskeletal pain who have been identified to be at risk for sickness absence?

Q2: Do patients participating in the PREVSAM model report higher work ability, improved pain status, better self-efficacy, less physical disability or higher health-related quality of life, compared with those who receive treatment as usual at follow-up?

Q3: Is there a patient-reported reduced risk (using the ÖMPSQ score) for sickness absence in patients participating in the PREVSAM model, compared with those who received treatment as usual at follow-up?

Q4: Can any effects be seen in regard to anxiety and depression symptoms or drug consumption in patients participating in the PREVSAM model, compared with those who receive treatment as usual?

Q5: Is the PREVSAM model more cost-effective compared with treatment as usual?

The study hypothesis is that a person-centred rehabilitation, illuminating and emphasizing responsibilities, using interdisciplinary teamwork which can also include collaboration with the employer and/or workplace, in an early stage before symptoms are manifest and consequences in form of sickness absence have become established, will be more effective than treatment as usual in prevention of sickness absence.

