### Intervention: the PREVSAM model (intervention group)

The PREVSAM model includes:
a person-centred approachidentification of the patient’s attitudes towards responsibility for the management of musculoskeletal pain and clarification of responsibilities for the individual, health care, employer/Swedish public employer servicestructured, individualised, synchronised, rehabilitation based on interdisciplinary teamwork, continuous communication and regular coordination among all stakeholders, and a mutual philosophy of rehabilitationearly access to psychologist or psychotherapist to address psychosocial factorspossibility of early contact and collaboration with employer/workplace before sickness absence has occurred.

The person-centred approach entails planning the rehabilitation together in partnership with the individuals, and taking their resources and wishes into consideration [27]. Individualised, person-centred, rehabilitation within the PREVSAM model will be based on the patient’s narrative and constructed together with the interdisciplinary team based on the patient’s goals, attitudes of responsibility, and physical, psychological, and social resources. Workplace preconditions will be assessed, preferably based on the Convergence Dialogue Meeting [28] also used in a previous rehabilitation study [29], and employer responsibility will be highlighted, based on the Organisational and social work environment provisions from the Swedish Work Environment Authority (AFS 2015:4). Responsibilities for the different parts of the participant’s rehabilitation will be clearly assigned to the individual, health care, and employer or Swedish public employer service.

The interdisciplinary team is an important component of the PREVSAM model and will be comprised of the patient, a physiotherapist, an occupational therapist, and a psychologist/psychotherapist. If needed, contact with a general practitioner will be provided. If orthopaedic consultation or further investigations are needed, the participant can be referred to a physiotherapist with experience in orthopaedic triage for assessment and further management.

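### Drug consumption related to the musculoskeletal condition is specified only as ATC main groups M and N, which mixes pain drugs with unrelated nervous-system drugs (minor, one secondary outcome)

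*Protocol article*

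**What the plan says.** The Drug consumption section of the protocol article states its target as "Consumption of pharmaceutical drugs that can be related to the musculoskeletal condition for which the participant is treated". In the same sentence it gives the operational content, in brackets, and the source: "ATC codes M – musculoskeletal system and N – nervous system) will be estimated using data from the Swedish registry for drug use", with filled prescriptions as the data. On timing it says "Data will be collected for a 3-month period before baseline and for the 12-month period after baseline". A second source follows: "Self-reported drug consumption, both prescription and nonprescription drugs, will be collected via the questionnaire".

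No section names an ATC subgroup, applies an indication filter, or says that M and N will be reported apart.

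The research question is Q4 under Aims: "Can any effects be seen in regard to anxiety and depression symptoms or drug consumption in patients participating in the PREVSAM model", compared with treatment as usual. It names drug consumption in general and pairs it with anxiety and depression symptoms.

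The intervention section lists early "access to psychologist or psychotherapist to address psychosocial" factors among the components of PREVSAM. Table 2 describes seeing such a professional under treatment as usual only as something that could be possible. Table 1 excludes severe mental illness and ongoing substance abuse, but not milder anxiety or depression, and HADS is itself a secondary outcome.

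**The concern.** The target and the code set do not match. The target is medication linked to the musculoskeletal condition. On the protocol's own label, group N is the nervous system. That takes in the analgesics the trial needs, but also drugs with no link to the condition, such as psychotropics. The register source as described is filled prescriptions, with no indication mentioned, so nothing in the stated definition restores the link.

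Two consequences follow for an outcome computed on M and N together. First, unrelated prescriptions add noise and shrink any difference in related medication. Second, if access to a psychologist or psychotherapist changes psychotropic prescribing in the intervention arm, that change enters the same measure. It could then be reported as a change in medication for the musculoskeletal condition, or could offset one.

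**Working it through.** The documents give no rate, variance, effect size or power for drug consumption, so there is no stated figure to reproduce. The mismatch itself is shown by setting the passages side by side; the arithmetic only illustrates direction and rough size.

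**Side by side**

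- Intended scope: drugs that can be related to the treated condition (Drug consumption).
- Stated codes: main groups M and N, with no subgroup (same sentence).
- Source: filled prescriptions, with no indication mentioned (same sentence).
- Population: only severe mental illness and ongoing substance abuse are excluded (Table 1), so some psychotropic use is plausible.
- Intervention: early psychologist or psychotherapist access in PREVSAM, at most possible under treatment as usual (intervention section, Table 2).
- Contrast: for sick leave, the Statistical analyses section retrieves all causes but singles out musculoskeletal disease as the part of special interest. No such split is made for drugs.

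**Illustration**

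From the documents: 200 per group and a significance level of 0.05 (Statistical analyses). Two-sided testing is assumed. All prescription rates below are assumptions.

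Take as endpoint any M or N prescription in the follow-up year. Let p be the probability of a related drug and u the probability of an unrelated N drug, independent of each other. Then

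P(any) = 1 − (1 − p)(1 − u).

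Power is Φ{(|Δ| − 1.96·SE₀)/SE₁}, with SE₀ the pooled and SE₁ the unpooled standard error of the difference in proportions.

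*Dilution.* With u equal in both arms, Δ = (p_TAU − p_PREVSAM)(1 − u). Whatever the values of p, the difference shrinks by the factor 1 − u. Assume p = 50% against 35%:

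| u in both arms | Any M/N, TAU v PREVSAM | Difference | Power |
|---|---|---|---|
| 0% | 50.0% v 35.0% | 15.0 points | 86% |
| 10% | 55.0% v 41.5% | 13.5 points | 77% |
| 20% | 60.0% v 48.0% | 12.0 points | 67% |
| 30% | 65.0% v 54.5% | 10.5 points | 57% |

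*Misreading.* Let related-drug use be 40% in both arms, so there is no effect on it. Then Δ = (1 − 0.40)(u_TAU − u_PREVSAM):

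| u, TAU v PREVSAM | Difference in any M/N | Chance of significance in that direction |
|---|---|---|
| 20% v 20% | 0 | 2.5% |
| 20% v 15% | 0.60 × 0.05 = 3 points | 9% |
| 25% v 15% | 0.60 × 0.10 = 6 points | 22% |
| 30% v 15% | 0.60 × 0.15 = 9 points | 44% |

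The first row shows that unrelated use alone causes no bias. A difference arises, beyond chance, only if the intervention itself shifts unrelated use.

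**The case against.** The strongest reply is that the protocol never says all of M and N, nor that they will be summed. The words about drugs that can be related to the condition may act as a restriction within those groups, and a subgroup list could well sit in an analysis plan or full protocol that is not shown. Because the codes identify the drugs, the data can still be split later. This stands in part. It rules out saying that the trial will certainly pool everything. It does not remove the point: the article does not leave the codes open but states them, more broadly than its own purpose, and gives no rule for narrowing them.

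A reader might infer that Q4 asks about pain medication and so cannot be answered. The documents do not support that. Q4 asks about drug consumption beside anxiety and depression symptoms, so psychotropic use may be of interest in its own right. That is a reason to report it separately, not to call the question unanswerable.

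A reader might also infer a collapse in power. Suppose a 12-month daily-dose total with mean 60 and SD 70, a reduction of 20, and 5%, 10% or 15% of participants on an unrelated daily drug (365 doses). A simple comparison of means then falls from 82% power to 47%, 34% or 27%. Every one of those inputs is invented, and the test is not the one described. The Statistical analyses section plans differences from baseline, with parametric or non-parametric tests according to the distribution. With stable use differenced out on rate-matched periods and 3% to 10% starting or stopping such a drug (180 doses), the same assumptions give 74% down to 60%. A rank test on the 12-month total, simulated with skewed data, gives roughly 75%, 66% and 59%. The direction survives; the large figures do not.

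Finally, randomisation balances unrelated drug use in expectation, so misattribution needs either chance or a true effect of PREVSAM on psychotropic use. In the latter case the change in consumption is real, and the error lies in its label. The pre-baseline window and the self-report help, but the first does not deal with drugs started or stopped after baseline, and the second is a separate measure from unblinded participants.

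**Conclusion.** The point holds as a minor one. The only operational definition given is broader than the stated target, so an outcome built on it mixes musculoskeletal-related drugs with unrelated nervous-system drugs. Dilution follows directly: under independence and equal unrelated use u, the difference in any use shrinks by 1 − u. Misreading a psychotropic change as a change in pain medication is possible, because the intervention includes early psychological care, but the documents give no figure for its likelihood.

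The conclusion rests on two things: that no narrower list is fixed elsewhere, and that group N, as its label indicates, reaches beyond pain drugs. That it includes psychotropics is general knowledge of the classification and not stated in the protocol. No size can be derived from the documents, and all power figures above are illustrations on assumed inputs. One secondary outcome is affected; the primary outcome and the sample size are not.

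**What to change.** Before the register extract is analysed, amend the Drug consumption section, or the corresponding analysis plan text, in two respects:

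- Define the musculoskeletal drug outcome by a fixed list of the pain-relevant subgroups of M and N: anti-inflammatory drugs, muscle relaxants, and analgesics including opioids.
- Report the psychotropic subgroups of N as a separate outcome beside HADS, in keeping with the way Q4 pairs drug consumption with anxiety and depression symptoms.

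If such a list already exists in an unpublished document, referring to it is enough. The cost is about one sentence; no new data and no participant burden are needed, since the outcome is already specified by ATC code. The small downside is that drugs with both pain and psychiatric uses must be assigned to one list in advance.

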### Statistical analyses

Primary outcomes are sickness absence and sick days, where the first outcome is binary and the second one is continuous and most likely skewed [47]. Sick leave regardless of reason will be retrieved. However, sick leave for diseases of the musculoskeletal system and connective tissue is of specific interest. Sample size calculations will be based on the general assumptions that we want a power of 80% and that statistical significance is set to α = 0.05. For the outcome sickness absence, the difference between the proportion of sickness absence = yes/no will be compared between the intervention (PREVSAM model) and control (TAU) group. We assume that approximately 30% in the control group will have sickness absence = yes at least one time during the 12 month follow-up period [48]. If the percentage of sickness absence = yes in the intervention group is assumed to be 15% or 20%, then the sample size in each group needs to be 312 individuals and 132 individuals, respectively. To detect a difference of 15% (30% with sickness absence in control group and 15% with sickness absence in intervention group), a total sample size of 264 (132 individuals in each group) would give approximately 80 cases to analyse for the primary outcome sick days. This would enable us to estimate 8 parameters in a logistic regression analysis. This would mean a power of about 75% to detect a difference of at least 0.6 Ln (sick days), if the standard deviation for Ln (sick days) is assumed to be 1. This is equal to a scenario with mean sick days of about 35 in the intervention group (PREVSAM model) and 68 in the control group (TAU). This would enable us to perform linear regression analysis adjusting for several covariates and estimating about 7 parameters. To summarise these calculations and allowing for dropouts, randomisation of 200 individuals to each group is required. An interim analysis will be performed for the primary outcome when 50% of patients have been randomised and have completed the 12 months follow-up. At the same time-point it might be possible to perform the short-term follow-up analyses. The interim analysis will be performed by a statistician, blinded to the treatment allocation. The statistician will report and discuss the results of the interim analysis with the steering committee in a joint meeting. The steering committee decides on the continuation of the trial.

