Group characteristics will be presented as mean and standard deviations, median and 25th and 75th percentile or the number and percentage. For the primary outcomes descriptive analyses for sickness absence for the two groups will be presented according to recommendations [31]. The sickness absence will be presented with number of individuals who had sickness absence during the follow-up period. Proportions of individuals with sickness absence per month will be presented. The number of sick days (gross and net) with sickness benefit during the follow-up periods will be presented with mean and median values. For participation in work life additional measures will be presented with descriptive statistics regarding time to sick-leave spell for musculoskeletal pain. Number of days before a sick leave spell > 14 days occurs and number and duration of sick-leave spells per individual will be presented for gross and net days. Outcomes will be analysed according to intention-to-treat. Multivariable logistic regression analysis will be used for the primary outcome sickness absence during the follow-up period [1], not being sickness absent (0) adjusted for confounders. Multivariable linear regression analyses, or possibly quantile regression, will be used to evaluate differences between groups for sick leave days, among those have at least one sick leave spell. All other measurements will be analysed by calculating raw differences between baseline and follow-up assessments. Parametric and non-parametric tests will be used depending on data level and distribution. Sub-group analyses can be performed in regard to characteristics of interest, such as diagnosis or sick-leave. The level of significance is set to *p* < 0.05. Relevant statistical programs will be used for the statistical analyses, for example the IBM SPSS, SAS, STATA.

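### The general raw-difference rule does not suit register drug data collected over 3 months before and 12 months after baseline unless both windows are put on one time scale

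*Protocol article*

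**What the plan says.** Drug consumption is a secondary outcome in the protocol article and is named in research question Q4 of the Aims: "Can any effects be seen in regard to anxiety and depression symptoms or drug consumption in patients participating in the PREVSAM model", set against treatment as usual.

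The Drug consumption section names two sources. Register consumption "will be estimated using data from the Swedish registry for drug use, regarding filled prescriptions", for ATC groups M and N, and on the windows: "Data will be collected for a 3-month period before baseline and for the 12-month period after baseline". The second source is the questionnaire: "Self-reported drug consumption, both prescription and nonprescription drugs, will be collected via the questionnaire". No unit is given for the register measure (total, daily doses, rate, or any use).

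The Statistical analyses section sets out models for the primary outcomes and then one rule for the rest: "All other measurements will be analysed by calculating raw differences between baseline and follow-up assessments". It adds "Parametric and non-parametric tests will be used depending on data level and distribution". Drug consumption is not excepted. No conversion to a rate and no baseline adjustment is stated for these outcomes.

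**The concern.** The only register data that can serve as a baseline cover 3 months, and the follow-up data cover 12. If the general rule is applied to the two totals as collected, amounts over periods that differ fourfold in length are subtracted. The result mixes change in use with the length of the window.

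Two things are at stake. The within-arm figures could show a sharp rise in analgesic and nervous-system drugs even where use fell. The subtraction would also give the baseline an arbitrary weight in the comparison between arms, so that it may do little of the work for which a baseline is collected.

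**Working it through.** The article gives no effect size, power or sample size for drug consumption, so there is no figure to reproduce.

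**Inputs.** Windows of 3 and 12 months (Drug consumption). Raw difference, follow-up minus baseline (Statistical analyses). For group size: "randomisation of 200 individuals to each group is required". Assumed, because the article gives no rates: r is the monthly rate before baseline, and k is the follow-up rate divided by the pre-baseline rate.

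**One participant, totals subtracted.** Difference = 12kr − 3r.

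- Unchanged use, k = 1: 12r − 3r = +9r. The ratio of totals is 12/3 = 4, a 300% rise.
- Use halved, k = 0.5: 6r − 3r = +3r, an apparent doubling.
- Zero difference: 12kr = 3r, so k = 0.25. Only a fall of more than 75% gives a negative difference.
- On a monthly scale, 3r/3 = r and 12kr/12 = kr. The difference is (k − 1)r, which is 0 for unchanged use.

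**Chance imbalance between arms.** Let the arms differ by d in the 3-month total, with the same k in both and no treatment effect. The 12-month totals then differ by 4kd. The raw difference subtracts 1 × d. A difference of rates, expressed in 12-month units, subtracts 4 × d.

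| k | Imbalance in 12-month total | Left by raw difference | Left by difference of rates (12-month units) |
|---|---|---|---|
| 1 | 4d | 3d | 0 |
| 0.5 | 2d | d | −2d |
| 0.25 | d | 0 | −3d |

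With stable use, 3d is 3/4 = 75% of the imbalance in the 12-month total, and three times the imbalance measured at baseline. The table also shows that rescaling alone does not secure good adjustment: if use falls, a difference of rates over-corrects. The two leave equal amounts when 4k − 1 = 4 − 4k, that is k = 0.625. Below that, the raw difference leaves less. A baseline covariate avoids both fixed weights (1 or 4) because its coefficient is estimated from the data.

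**Simulation of the stable case.** Assumed: 200 per arm, individual monthly rates from a gamma distribution (shape 0.5, scale 2) constant over time, Poisson dispensings, no treatment effect, 4,000 runs.

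| Quantity | Raw totals | Rates × 12 | 12-month total alone |
|---|---|---|---|
| Slope of the arm difference on the imbalance in monthly rate | 8.97 (expected 12 − 3 = 9) | −0.07 (expected 0) | 11.99 (expected 12) |
| SD of the arm difference | 1.32 | 0.78 | 1.72 |

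The mean arm difference for raw totals was −0.004, which is no bias. The variance ratio of raw totals to rates is (1.32/0.78)² ≈ 2.9. Covariate adjustment was not simulated.

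**The case against.** The strongest objection is that the subtraction of totals is inferred. The Drug consumption section fixes an extraction period, not an outcome variable. The general rule speaks of assessments, and in the Data collection section baseline and the 1-, 3-, 6- and 12-month follow-ups are questionnaire time points. The rule fits self-reported drug use with no window problem. It also cannot be exhaustive if read literally, since cost-effectiveness ratios and the proportion scoring below 40 on the screening questionnaire are not baseline-to-follow-up differences. How dispensings are scaled could properly be set in an analysis plan that is not shown. All of this stands, and it is why the point is conditional and minor. It does not remove the point: the one rule stated covers all other measurements, calls the differences raw, and does not suit these windows.

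A reader might infer more in three ways, and the documents do not support any of them.

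- *That the answer to Q4 will be biased.* Q4 compares arms, and the window effect is common to both under randomisation.
- *That three-quarters of any baseline imbalance remains.* The 75% refers to the imbalance in the 12-month total and holds only if use is stable. Table 1 admits people with less than 3 months of pain in the current episode, so constant use over 15 months is an illustration, not an expectation.
- *That the windows must be made equal by extracting 12 months before baseline.* At least 12 − 3 = 9 of those months would precede the current episode, so this is not clearly a better baseline.

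**Conclusion.** The point holds in a limited form. The general rule is a poor fit for the register drug data as the article describes them. If totals are subtracted, the within-arm change is misleading at any fall short of 75%. The comparison between arms remains valid on average but adjusts badly for chance imbalance and, in the stable-use illustration, has about 2.9 times the variance of a comparison on a common scale. That last figure rests on assumed rates and on no change in use over time. With a marked fall in use, simple rescaling of the difference would lose its advantage, which is why the covariate matters as well as the scale. The outcome is secondary and the point is minor.

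**What to change.** In the Drug consumption or Statistical analyses section, state that register consumption is expressed per month (or per 3 months) in both windows, and that arms are compared on the follow-up rate with the pre-baseline rate as covariate, in place of the raw difference. The common scale makes the descriptive change readable, and the covariate handles the chance imbalance. In a linear model the scale of the covariate does not alter the test of treatment, so the two parts do not conflict. Say also that the raw-difference rule, if kept elsewhere, does not apply to these register data.

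The cost is about one sentence and one derived variable: the pre-baseline total divided by 3 and the follow-up total divided by 12. No new data are needed. If follow-up is to be shown in 3-month slices as well, dispensing dates are needed.
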